
### Outcomes

Participants will complete outcome measures at baseline, 6 and 12 months, administered by practice staff blinded to participant allocation, which are from the standardised outcome measurement for patients with coronary artery disease, agreed by the International Consortium for Health Outcomes Measurement^14^ (tables 1 and 2). The primary outcome will be the UK Version of Seattle Angina Questionnaire (SAQ-UK) Physical Limitation domain^15^ assessed at 12 months’ follow-up. Participants completed secondary outcomes will include the remaining two domains of the SAQ-UK,^15^ Medical Research Council (MRC) dyspnoea scale,^16^ Hospital Anxiety and Depression Scale^17^ and General Self-Efficacy Scale.^18^ Physical activity will be measured where possible with the ActivPAL accelerometer^19^ for 7 days, supplemented by the International Physical Activity Questionnaire.^20^ Cardiovascular fitness will be measured with the Incremental Shuttle Walk Test.^21^ Economic measures will be EuroQol-5 Dimensions-5 Levels (EQ-5D-5L)^22^ and Client Service Receipt Inventory (CSRI)^23^ as well as intervention costs. Baseline assessments will also include height, weight, blood pressure and serum cholesterol within the last 12 months.

**Table 1 T1:** ACTIVATE outcome measures

Patient completed measure—primary	Description	Range
UK version of Seattle Angina Questionnaire (SAQ-UK) Physical Limitation domain^15^	Measures how daily activities are limited by angina over the past 4 weeks. Items are weighted equally, summed and transformed to a 0–100 score. Higher score indicates better functioning.	(0–100)
Patient completed measures—secondary		
SAQ-UK Angina Frequency and Perception and Treatment Satisfaction domains^15^	Remaining two domains of SAQ-UK. Items are weighted equally, summed and transformed to a 0–100 score. Higher scores represent higher levels of health or satisfaction with treatment.	(0–100)
MRC dyspnoea scale^16^	Five item questionnaire that assesses the degree of shortness of breath with common activities. One point is assigned to each activity associated with dyspnoea. Higher scores indicates more limitation due to dyspnoea.	(0–5)
Hospital Anxiety and Depression Scale^17^	Measures anxiety (seven items) and depression (seven items) in patients with physical health problems. Two subscales with higher scores indicating greater anxiety or depression.	(0–21)
General Self-Efficacy scale^18^	Measures optimistic self-belief to cope with a variety of difficult demands in life. Higher score indicates greater self-efficacy.	(10–40)
International Physical Activity Questionnaire^20^	This questionnaire supplements the accelerometer data by providing self-reported duration (minutes) and frequency (days) of physical activity in the previous 7 days in the domains: job related, transportation, housework, recreation and sitting.	Minutes of light, moderate and vigorous physical activity
Patient Completed Economic Measures		
EQ-5D-5L^22^	Health utility index with five dimensions (mobility, self-care, usual activities, pain/discomfort, anxiety/depression) and five levels to give health states converted to a utility weight. Also Visual Analogue Score (VAS) for health state today	Health utility weight from 0 (death) to 1.0 (perfect health) also with negative values VAS (0–100)
Client Service Receipt Inventory^23^	Collects information about health service use, including medication, smoking cessation, diet management, weight control programmes and exercise referral schemes.	According to activity
Objective measures of physical activity and function		
Physical activity measured with the ActivPAL accelerometer^19^	The ActivPAL device is a small, slim monitor worn on the thigh. It provides accelerometer-derived information about thigh position and acceleration to determine body posture (sitting, lying or upright), stepping and stepping speed (cadence), from which energy expenditure can be inferred. It will be worn for 7 days to measure step count, energy expenditure, duration of sedentary, light, moderate and vigorous physical activity. Participants will be asked to keep a wear diary documenting working hours, sleep, removal reasons and any other comments.	Step count, energy expenditure, duration of sedentary, light, moderate and vigorous physical activity
Incremental Shuttle Walk Test^21^	Progressive walking test that requires the participant to walk up and down a 10 m course, at a speed dictated by an audio signal. The time between signals is reduced every minute and there are 12 levels. The test ends when the participant either (a) is too breathless to maintain the required speed or (b) fails to complete a shuttle in the time allowed or (c) reaches 85% of the predicted maximal heart rate.	Metres walked

EQ-5D-5L, EuroQol-5 Dimensions-5 Levels; MRC, Medical Research Council.

**Table 2 T2:** ACTIVATE protocol schedule of forms and procedures

Procedures	Screening	Baseline/randomisation	7 days postrandomisation*	Trial intervention†	26 weeks postrandomisation	27 weeks postrandomisation*	52 weeks postrandomisation	53 weeks postrandomisation*
Eligibility screening and consent								
Assessment of eligibility	X							
Informed consent	X							
Confirm consent		X		X	X		X	
Randomisation		X						
Vital signs, height, weight, serum cholesterol		X						
Outcome measurement								
Seattle Angina Questionnaire		X			X		X	
MRC dyspnoea scale		X			X		X	
Hospital Anxiety and Depression Scale		X			X		X	
General Self-Efficacy scale		X			X		X	
EQ-5D-5L		X			X		X	
Client Service Receipt Inventory		X			X		X	
Physical activity measured with ActivPal accelerometer		X	X*		X	X*	X	X*
International Physical Activity Questionnaire			X			X		X
Incremental shuttle walk test		X			X		X	
Safety event reporting								
Monitoring of adverse events			X	X	X	X	X	X
Monitoring of serious adverse events			X	X	X	X	X	X

*Removal of ActivPal after 7 days.

†If randomised to intervention arm, participants will be invited to meet with member of cardiac rehabilitation staff who will train the participant on how to use the intervention.

EQ-5D-5L, EuroQol-5 Dimensions-5 Levels.

Qualitative interviews will take place with a selection of participants at the end of the 12-week cardiac rehabilitation programme among those receiving the intervention, and between months 11 and 12 with the same sample of participants in the intervention group and an additional sample from the control group. These will gather data on trial participation and intervention design (see the ‘Process evaluation’ section).

Routinely collected demographic, clinical and recruitment data will include the number of participants who are eligible, willing to be randomised, withdraw after randomisation, complete outcome measurements, reasons for non-completion, age and gender.

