#### Randomisation procedures

Participants will be randomised via a secure (24-hour) web-based randomisation system controlled centrally by the clinical trials unit to receive either usual care or tailored cardiac rehabilitation programme (‘Activate Your Heart’) plus usual care. Randomisation will have an allocation ratio of 1:1 and use a minimisation programme with a built-in random element, stratified by site and gender. Randomisation should occur no more than 2 weeks after confirming eligibility, obtaining informed consent and completing baseline assessments. Following allocation, participants will be notified of their allocation as soon as possible and then receive their randomised treatment allocation.

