#### Blinding

This is a pragmatic trial comparing the ‘Activate Your Heart’ cardiac rehabilitation intervention with usual care, so it will not be possible to blind participants or their rehabilitation providers to treatment group allocation. However, collection of outcome measures and data analysis will be performed blind to treatment allocation. We will include a perception of allocation form for the person collecting the outcome measures to complete, to monitor the level of blinding achieved for these researchers.

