#### Analysis of effectiveness

Primary and secondary outcomes at baseline, 6 months’ and 12 months’ follow-up will be summarised for each treatment group using descriptive statistics at each time point. If normally distributed, the difference between group means (with 95% CIs) will be reported from an analysis of covariance (ANCOVA) adjusted for baseline score and stratification factors.

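### As Table 2 schedules them, the first ActivPAL week and first IPAQ fall after randomisation, contrary to the Randomisation procedures section, so the physical-activity outcomes have no pre-randomisation baseline score

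*Protocol article*

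**What the plan says.** Table 1 says of the accelerometer: "It will be worn for 7 days to measure step count, energy expenditure, duration of sedentary, light, moderate and vigorous physical activity". It describes the IPAQ as giving "self-reported duration (minutes) and frequency (days) of physical activity in the previous 7 days".

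Table 2 marks the ActivPAL in the baseline/randomisation column and in the column for 7 days after randomisation, with the footnote "Removal of ActivPal after 7 days". The row for the "International Physical Activity Questionnaire" is marked only at 7 days, 27 weeks and 53 weeks after randomisation. The other outcome measures (SAQ-UK, dyspnoea, anxiety and depression, self-efficacy, EQ-5D-5L, service use, shuttle walk) are all marked in the baseline/randomisation column.

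The Randomisation procedures section gives a different order: "Randomisation should occur no more than 2 weeks after confirming eligibility, obtaining informed consent and completing baseline assessments". It continues: "Following allocation, participants will be notified of their allocation as soon as possible and then receive their randomised treatment allocation". The Blinding section accepts that "it will not be possible to blind participants or their rehabilitation providers to treatment group allocation".

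The Analysis of effectiveness section covers primary and secondary outcomes and, for normally distributed ones, specifies an "analysis of covariance (ANCOVA) adjusted for baseline score and stratification factors". The Mediation analyses section names physical activity as one of two hypothesised mediators of the primary outcome.

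**The concern.** A baseline covariate is safe in ANCOVA because randomisation makes it independent of arm. A value recorded after participants have learned their arm loses that guarantee. In an open trial of a programme that promotes exercise, people told they will receive it may become more active at once, and controls may react in either direction. The IPAQ is also self-reported. If week-1 activity differs by arm for such reasons, adjusting for it removes part of the treatment effect, or adds to it.

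At stake are the ActivPAL and IPAQ secondary outcomes, and the mediation analysis if it uses this value as baseline activity. An analysis plan can decline to use the covariate, but it cannot supply a pre-randomisation measurement that the schedule never collects.

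**Working it through.** **No stated figure is in dispute.** The sample size concerns the SAQ-UK primary outcome and reproduces: a difference of 8 with SD 25, 5% two-sided and 90% power gives 206.19, so 207 per group by t-test; 207/0.8 = 258.75, so 259 per group and 518 in total.

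**Timing (Tables 1 and 2).** Start day = collection day − length of record.
- ActivPAL: removed on day 7 after 7 days' wear; 7 − 7 = day 0.
- IPAQ: completed on day 7 with a 7-day recall; 7 − 7 = day 0.

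Both windows run from day 0 to day 7 after randomisation. Suppose the device were attached k days before randomisation, which the 2-week window permits. Removal at day 7 would then come k + 7 days after attachment, which agrees with the footnote only if k = 0. The IPAQ window does not depend on k.

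**Bias.** Let b be true pre-randomisation activity, T the arm (0 or 1), τ the true later effect and β the within-arm slope of later on early activity:

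y = a + τT + βb + e.

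If the recorded value is b* = b + d0·T, substituting b = b* − d0·T gives

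y = a + (τ − β·d0)T + βb* + e.

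ANCOVA therefore estimates τ − β·d0. Writing d0 = f·τ, where f is the share of the later effect already present in week 1, the estimate is τ(1 − βf) and the proportional attenuation is βf.

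The documents give neither β nor f. The ranges below are assumptions.

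| f | β = 0.5 | β = 0.7 |
|---|---|---|
| 0 | 0% | 0% |
| 0.10 | 5% | 7% |
| 0.25 | 12.5% | 17.5% |
| 0.50 | 25% | 35% |

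If week 1 moves against the later effect, f is negative and the estimate is inflated: f = −0.25 with β = 0.5 gives +12.5%.

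**Illustration in SD units.** Assume τ = 0.32 SD (borrowed from the primary outcome, 8/25, because no activity effect is given), equal SDs so that β is the correlation, 207 per arm and d0 = 0.1 SD (f = 0.1/0.32 = 0.31). The standard error is √((1 − β²) × 2/207).
- β = 0.5: 0.32 − 0.05 = 0.27 SD (16% attenuation); power falls from 96.4% to 88.7%.
- β = 0.7: 0.32 − 0.07 = 0.25 SD (22% attenuation); power falls from 99.5% to 94.5%.

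Simulation with 1,000,000 participants per scenario gave 0.272 and 0.252, in agreement with the formula.

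**The case against.** The strongest reply is that no influence of treatment on week 1 has been shown. Table 2 places the trial-intervention column after the 7-day column, and the Cardiac rehabilitation intervention section requires a staff contact before the programme begins. On that order the first activity week may precede the programme, leaving only a reaction to knowing the arm, of unknown size and possibly nil. This stands. It also makes f = 0.50 implausible, because half of the later effect would have to appear within a week, in a graded programme that takes about 8 weeks. It does not remove the exposure: no date is fixed for the staff contact, and participants are told their arm promptly.

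Second, the Randomisation procedures section may govern and the 7-day column heading may be loose. That is possible for the ActivPAL. It does not help the IPAQ, which has no baseline mark at all. The same attach-then-collect pattern recurs at 26/27 and 52/53 weeks, so the layout looks intended. Either way the two places conflict.

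Third, the Analysis of effectiveness section refers only to a baseline score, conditional on normality, and never names the week-1 record as that score. This also stands: its use is the natural consequence of a schedule with no other early activity value, not an explicit instruction.

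Fourth, the mediation analysis runs only if the primary result is significant, and the article does not say that it adjusts for baseline activity. A reader might infer that mediation necessarily inherits the bias; the text does not support that.

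**Conclusion.** The contradiction between Table 2 and the Randomisation procedures section is real. If Table 2 is literal, the ActivPAL and IPAQ outcomes have no pre-randomisation value, and the baseline-adjusted ANCOVA could use only one that is open to influence from knowledge of allocation. The bias is −slope × d0: zero with no week-1 difference between arms, and 0–35% attenuation over the assumed ranges (slope 0.5–0.7, f 0–0.50), with the upper end unlikely. It reverses direction if week 1 moves against the later effect.

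A reader might go further and conclude that these baselines are contaminated by treatment, or that the trial's main result is at risk. The documents support neither. The column order and the required staff contact make influence possible, not demonstrated. The SAQ-UK primary outcome, the other questionnaires and the shuttle walk are scheduled at the baseline visit and are unaffected. The mediation analysis is touched only if it uses the week-1 value as baseline activity. This is a moderate issue for secondary outcomes, not one on which the trial's main conclusion depends.

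**What to change.** Reconcile Table 2 with the Randomisation procedures section: attach the ActivPAL at the baseline visit, complete the 7-day wear and the IPAQ, and then randomise. The 2-week window already allows this. The cost is a schedule amendment, about one week's delay to each randomisation, and device removal and IPAQ completion before allocation. The Trial status section reports 68 recruited at submission, so a change at that point could have covered up to 518 − 68 = 450 participants (87%).

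For participants already randomised under the current schedule:
- label week-1 activity as an early follow-up measure and do not use it as a covariate in the activity models, or as baseline activity in the mediation analysis;
- keep these participants in the activity models with baseline activity treated as missing, handled identically in both arms;
- adjust for pre-randomisation variables such as baseline shuttle walk distance and SAQ-UK.

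The cost for these participants is precision. With no activity covariate the standard error rises by a factor of up to 1/√(1 − slope²), which is 1.15 at a slope of 0.5 and 1.40 at 0.7. Adjustment for the other baseline variables should recover part of this.

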### Sample size

In order to detect the minimum clinically important difference of 8 points for the SAQ-UK physical limitation domain, assuming an SD of 25,^15^ with 90% power at the 5% significance level, 207 participants per group will be required (calculated using nQuery 8). In order to allow for up to 20% loss to follow-up, we aim to recruit 259 participants per group (518 in total). This sample size will give >99% power for secondary outcomes.

### Recruitment and randomisation

#### Screening and consent

Written informed consent will be sought from potential participants who will be approached by the study team and invited to consider participation, following a search of their health record for eligibility. Where possible, potential participants will be introduced to the study during a face-to-face appointment with clinical staff. Potential participants can also be approached by a member of the local research team by written invitation and followed up by a phone call or text message after a week if there has been no response. Potential participants will be invited to attend a screening appointment. If they are eligible, and interested in the trial, the trial team researchers would then recruit participants following the trial’s informed consent process. These assessments will be recorded in a screening log, including any reasons for ineligibility. Copies of the participant information sheet and informed consent form can be found in online supplemental appendix 2.

10.1136/bmjopen-2024-084509.supp2Supplementary data

#### Randomisation procedures

Participants will be randomised via a secure (24-hour) web-based randomisation system controlled centrally by the clinical trials unit to receive either usual care or tailored cardiac rehabilitation programme (‘Activate Your Heart’) plus usual care. Randomisation will have an allocation ratio of 1:1 and use a minimisation programme with a built-in random element, stratified by site and gender. Randomisation should occur no more than 2 weeks after confirming eligibility, obtaining informed consent and completing baseline assessments. Following allocation, participants will be notified of their allocation as soon as possible and then receive their randomised treatment allocation.

#### Blinding

This is a pragmatic trial comparing the ‘Activate Your Heart’ cardiac rehabilitation intervention with usual care, so it will not be possible to blind participants or their rehabilitation providers to treatment group allocation. However, collection of outcome measures and data analysis will be performed blind to treatment allocation. We will include a perception of allocation form for the person collecting the outcome measures to complete, to monitor the level of blinding achieved for these researchers.

### Statistical analysis

Final analysis will take place once all participants have been followed up for 12 months, and the database has been locked. Analyses will be by ‘intention to treat’ for the primary and secondary outcomes on all randomised participants, in the group to which they were allocated, and for whom the outcomes of interest have been observed or measured. A full and detailed statistical analysis plan (SAP) will be finalised prior to any comparative analysis of the groups; the main features of the SAP are described briefly here.

#### Baseline

Demographic and clinical characteristics will be summarised separately using descriptive statistics for each randomised group to allow assessment of whether balance was achieved between randomised groups. This will include gender, ethnicity, socioeconomic status and other relevant PROGRESS-Plus characteristics.^24^ No statistical testing of differences between groups will be performed.

#### Analysis of effectiveness

Primary and secondary outcomes at baseline, 6 months’ and 12 months’ follow-up will be summarised for each treatment group using descriptive statistics at each time point. If normally distributed, the difference between group means (with 95% CIs) will be reported from an analysis of covariance (ANCOVA) adjusted for baseline score and stratification factors.

#### Missing data and withdrawals

Predictors of missing data will be investigated using regression models (including age, living arrangements and comorbidities) and any significant predictors will be considered for inclusion in the models. In addition, given the two assessment points at 6 and 12 months, a sensitivity analysis will be conducted using a joint modelling approach to check whether there is any difference in outcome, using longitudinal outcome rather than the outcome at 6 months or 12 months alone, between the randomised arms, adjusted for dropouts or missing values.

#### Instrumental variable regression

The causal impact of engagement with the intervention will be assessed in an instrumental variable regression model, using the number of stages completed in the rehabilitation programme, and the number of times that the programme is accessed, as measures of intervention use.

#### Mediation analyses

The hypothesised mechanism of change for the rehabilitation intervention is that participants’ primary outcome (physical limitation) is mediated by self-efficacy and physical activity. If the rehabilitation intervention has a significant effect on the primary outcome (p<0.05) in ANCOVA, causal mediation analysis will be used to determine whether these potential mediators predict change in SAQ-UK Physical Limitation domain at 12 months.

### Economic analysis

The economic evaluation aims to estimate the cost-effectiveness of the ‘Activate Your Heart’ online rehabilitation programme plus optimal usual care when compared with optimal usual care alone. The rehabilitation programme will be fully costed using unit costs from a health service perspective. Unit costs will be obtained from national sources of reference costs and applied to information received from pilot questionnaires, namely salary band of cardiac rehabilitation therapists, time spent with the participant at the initial and final rehabilitation appointments, costs of travel and the costs of registering with the ‘Activate Your Heart’ online cardiac rehabilitation programme. Participants’ health service activity data will be obtained from the CSRI^23^ and unit costs from national sources.^25 26^ The costs of service use and the cost of the intervention will be added together for use in a cost-effectiveness analysis. We will account for the likely skewed nature of cost data in any regression carried out, by using Tweedie regression and/or beta distributions. The EQ-5D-5L scores will be converted into a health utility weight using UK norms. The base-case analysis will be conducted using the Van Hout scoring algorithm,^27^ with sensitivity analysis conducted using the EQ-5D-5L value set for England.^28^ Utility indices will be used to calculate QALYs over the 12-month trial period, using the area under the curve approach, with regression-based adjustment for baseline EQ-5D utility scores.^29 30^ The health economic results will initially be presented as disaggregated tables of costs alongside the health consequences. In these tables, we will also describe the costs and consequences of the rehabilitation intervention in the underserved groups recruited, such as women, ethnic minorities and those of low socioeconomic status.

Costs and consequences will then be combined in a cost–utility analysis, to estimate the cost per additional QALY gained associated with each of the compared options. Deterministic and probabilistic sensitivity analyses will be undertaken to explore the robustness of the obtained results to sample variability and plausible variations in key assumptions and employed analytical methods. Cost-effectiveness acceptability curves will be constructed to show the probability that the intervention is cost-effective at specific thresholds of cost per QALY gained such as NICE threshold range of £20 000–£30 000 per QALY gained.^31^ We will develop a two-stage economic model; a decision tree to reflect the outcomes of the trial (within-trial economic evaluation) and a Markov state transition model to extrapolate the evolution of patient outcome and costs over a lifetime horizon (model-based economic evaluation). Value of information analysis will be conducted after taking into account uncertainty derived from decision-analytical models.

